#### **5.5.4 Management of specific toxicity**

This section extracted and adapted from [23].

##### **5.5.4.1 Management of infections**

Sirolimus has immunosuppressive properties and may predispose patients to bacterial, fungal, viral or protozoal infections, including infections with opportunistic pathogens.

Investigators and caregivers should be aware of the increased risk of infection during sirolimus treatment. Pre-existing infections should be treated prior to starting with sirolimus. While taking sirolimus, symptoms and signs of infection should be monitored; if a diagnosis of infection is made, appropriate treatment should be given and interruption or discontinuation of sirolimus should be considered (see section 5.5.3, Table 6, section 7).

If ACTH for infantile spasms is used in the treatment group, antibiotic prophylaxis, e.g. with cotrimoxazole, should be considered.

If a diagnosis of invasive systemic fungal infection is made, discontinue sirolimus and treat with appropriate antifungal therapy.

##### **5.5.4.2 Management of skin toxicity**

For study participants with grade 1 toxicity, no specific supportive care is needed or indicated. A rash must be reported as an AE. Patients with grade 2 or higher toxicity should be treated with age-appropriate supportive measures at the discretion of the investigator.

##### **5.5.4.3 Management of stomatitis / oral mucositis / mouth ulcers**

Caregivers should be instructed to report the first onset of buccal mucosa irritation/reddening to their study team immediately.

Stomatitis/oral mucositis/mouth ulcers due to the study drug should be treated using local supportive care. Interruption or discontinuation of sirolimus should be considered (see section 5.5.3, Table 6, section 7).

##### **5.5.4.4 Management of diarrhea**

Appearance of grade 1-2 diarrhea attributed to study drug toxicity may be treated with supportive care at the earliest onset.

##### **5.5.4.5 Management of non-infectious pneumonitis**

Non-infectious pneumonitis is a class effect of rapamycin derivatives. Cases of interstitial lung disease (including pneumonitis, and infrequently bronchiolitis obliterans with organizing

|                                                                    |                                              |                                |
|--------------------------------------------------------------------|----------------------------------------------|--------------------------------|
| Clinical Trial Code: PROTECT
EU trial number: 2022-502332-39-00 | Trial Protocol
(Version 06; (01.10.2024)) | Page 63 of 110
CONFIDENTIAL |
|--------------------------------------------------------------------|----------------------------------------------|--------------------------------|

pneumonia [BOOP] and pulmonary fibrosis), with no identified infectious etiology have occurred in adult patients receiving immunosuppressive regimens including sirolimus. Some of these have been severe and on rare occasions, a fatal outcome was observed. In some cases, the interstitial lung disease has resolved upon discontinuation or dose reduction of sirolimus. These risks may increase with higher sirolimus trough levels. Individuals participating in this trial will be routinely assessed for the occurrence of new or changes in existing pulmonary symptoms consistent with lung toxicity. Consultation with a pulmonologist is recommended for any case of pneumonitis that develops during the study.

A diagnosis of non-infectious pneumonitis should be considered in patients presenting with non-specific respiratory signs and symptoms such as hypoxia, pleural effusion, cough, or dyspnea, and in whom infectious, neoplastic and other non-medicinal causes have been excluded by means of appropriate investigations. Caregivers should be advised to promptly report any new or worsening respiratory symptoms.

Consider corticosteroids if infective origin is ruled out. Taper as medically indicated.

### 5.5.5 Subject Compliance

Compliance is measured by the amount of study medication left in the medication bottles at each study visit.

Subject compliance will be assessed at each visit during the trial and will be verified by interviewing caregivers and through accounting of returned trial medication at each visit and the patient diary kept by the caregiver(s). Compliance will be recorded by measuring the amount of sirolimus returned at each study visit. The person responsible for the clinical trial medication calculates the amount of used medication by subtracting the unused clinical trial medication (in ml) from the total contents of the study medication bottles and comparing it with the documentation of administered medication. The amount of the unused medication and the documentation should be reliable and consistent (with a tolerance of 15%). Details will be recorded in the eCRF.

Inadequately low levels (under the detection level of the laboratory) given the administered dose and not otherwise explicable, e.g. by interindividual rates of metabolization, should raise the suspicion for reduced compliance

Non-compliance (i.e., missed or incorrect dosing) will be documented in the source data and the eCRF. In subjects and / or caregiver(s) of the subject who demonstrate non-compliance between visit intervals, the caregiver(s) of the subject will be counselled by trial staff to address reasons for non-compliance. If after counselling the subject and / or caregiver(s) of the subject continues to exhibit non-compliance over two consecutive trial visits, the subject should be withdrawn from the trial. Dosing interruptions of 7 days or more must be discussed with the sponsor.

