### 7.2 Permanent Discontinuation from Treatment with the IMP

Permanent treatment discontinuation with the IMP is any treatment discontinuation associated with the investigator's or the legal guardian(s) of the subject's definitive decision not to re-expose the subject to the IMP. The following criteria will lead to a permanent treatment discontinuation:

- Withdrawal of consent to trial participation
- Loss to follow-up
- Death
- Legal guardian(s)'s request, i.e. withdrawal of consent for treatment → documentation in source data
- Use of illicit drugs, prohibited concomitant medications (e.g. other mTOR inhibitors), or other substances that, in the opinion of the investigator, are likely to increase toxicity or otherwise confound the results while taking the IMP.
- Recurring grade 4 adverse events (AE) or serious and unexpected adverse events (SAE) related to the IMP require permanent discontinuation of sirolimus.

|                                                                    |                                              |                                |
|--------------------------------------------------------------------|----------------------------------------------|--------------------------------|
| Clinical Trial Code: PROTECT
EU trial number: 2022-502332-39-00 | Trial Protocol
(Version 06; (01.10.2024)) | Page 81 of 110
CONFIDENTIAL |
|--------------------------------------------------------------------|----------------------------------------------|--------------------------------|

- Lack of compliance, e.g. caregivers and participants fail to attend interim visits or to perform self-medication according to schedule.
- Any additional diagnosis due to which, in the investigator's opinion, participation in the treatment group of the trial may pose a risk for the study participant or that may interfere with protocol adherence.
- Negative Risk-Benefit Evaluation
- Subject did not meet in-/exclusion criteria (coming to light after inclusion), if it poses a risk for the study participant to continue the IMP in the opinion of the investigator.

The reason for the permanent discontinuation of treatment with IMP has to be documented in the source data.

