Even if the trial treatment with the IMP is discontinued, the subjects may remain in the trial and, given the legal guardian(s) oral agreement (documentation in source data), will be followed-up as outlined in the schedule of assessments (further study visits according to the control group) and section 6.

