### 7.3 Discontinuation of Trial

The following incidents will lead to discontinuation of a patient from the trial:

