#### 7.3.1 Withdrawal of Consent

Legal guardian(s) of the subjects may withdraw his/her/their consent to trial participation at any time without the need to justify the decision. If legal guardian(s) of the subject wants to withdraw his/her/their consent, the investigator should explain the difference between treatment discontinuation and withdrawal from trial participation, including the options for continued follow-up after discontinuation of the study medication (see section 7.2).

If the legal guardian(s)'s withdraw their consent for further study visits, they should be asked if they give their consent to take part at least in V12 (visit with 24 months of age) with respect to the primary endpoint measurement. The consent has to be as an additional agreement in written form on the last given written Informed Consent Form. 7.3.1

The withdrawal of consent has to be documented in the source data.

Usually, the legal guardian(s) of the subject's withdrawal of consent only relates to future information. Therefore, the sponsor may retain and continue to use any data collected before the withdrawal of consent.

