### 9.4 Primary Analysis

As **primary analysis**, the BSID-III cognitive scale of 2 years will be analysed using a two-sided Mann-Whitney-U-test ( $\alpha=0.05$ ) stratified by age groups (0-<2 and 2-<4 months of age) comparing the treatment versus the control group. The Mann-Whitney-U-test is used instead of the t-test because there are hints that the values could be not normally distributed in this

|                                                                    |                                              |                                |
|--------------------------------------------------------------------|----------------------------------------------|--------------------------------|
| Clinical Trial Code: PROTECT
EU trial number: 2022-502332-39-00 | Trial Protocol
(Version 06; (01.10.2024)) | Page 92 of 110
CONFIDENTIAL |
|--------------------------------------------------------------------|----------------------------------------------|--------------------------------|

population. All patients randomized will be evaluated following the treatment policy strategy (ICH E9 R1).

Missing values of patients (including missing values due to early termination of the study) without a BSID-III cognitive scale at the age of 2 years will be replaced

- a) with randomly selected values of patients in the control group (single imputation) if the 1-year value is not available
- b) with data of the control patients using a linear regression model with the 1-year value as independent variable and the 2-year value as the dependent variable (single imputation) if the 1-year value is available

Values of the control group will be used in order to achieve a conservative estimate. No fixed value is used for single imputation (e.g. the median) to reduce the risk to underestimate the variance. The seed to select values randomly is 4421360.

Additionally, the median of the BSID-III cognitive scale and the corresponding 95% CI will be displayed by group.

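### Section 5.5.5 withdraws persistently non-compliant children from the trial, against sections 7.2, 7.3 and 9.4, and so creates avoidable missing 24-month scores in the sirolimus arm only

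*Protocol*

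**What the plan says.** - **Section 5.5.5 (Subject Compliance).** Non-compliance is a matter of dosing: "Non-compliance (i.e., missed or incorrect dosing) will be documented in the source data and the eCRF". It is measured through the drug: "Compliance will be recorded by measuring the amount of sirolimus returned at each study visit". After counselling, if the child or caregiver "continues to exhibit non-compliance over two consecutive trial visits, the subject should be withdrawn from the trial".
- **Section 7.2 (Permanent Discontinuation from Treatment with the IMP).** The criteria for stopping the drug include "Lack of compliance, e.g. caregivers and participants fail to attend interim visits or to perform self-medication according to schedule". The section then adds: "Even if the trial treatment with the IMP is discontinued, the subjects may remain in the trial". With the guardians' oral agreement, follow-up continues on the control group's visits.
- **Section 7.3 (Discontinuation of Trial).** It opens with "The following incidents will lead to discontinuation of a patient from the trial" and has three entries: withdrawal of consent, loss to follow-up and death. Under withdrawal of consent, guardians who decline further visits are still approached about the primary endpoint: "they should be asked if they give their consent to take part at least in V12".
- **Section 9.4 (Primary Analysis).** "All patients randomized will be evaluated following the treatment policy strategy (ICH E9 R1"). A missing 2-year score is replaced by a randomly chosen control value if there is no 1-year score. If there is one, it is replaced by a prediction from a regression fitted in controls.
- **Sections 1.3.10 and 6.5.** After a negative risk-benefit evaluation the drug stops, and the child is followed to the primary endpoint.

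**The concern.** One event has two consequences in the same protocol: removal from the trial (5.5.5), or an end to the drug with follow-up possible (7.2). A site cannot apply both.

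The choice decides whether the primary endpoint is collected. A treatment-policy analysis needs the score actually observed at 24 months, whatever the adherence. Section 5.5.5 ends observation because of an intercurrent event that this strategy sets aside. There is no placebo and compliance is judged on sirolimus, so no control child can trigger the rule and any missing scores it causes fall in one arm. The request to attend V12 does not rescue these scores, because it is written only for guardians who withdraw consent. A child removed this way also drops out of the per-protocol set, which requires the 2-year BSID-III (section 9.1). The per-protocol sensitivity analysis therefore loses the child too.

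**Working it through.** **1. The texts side by side**

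| Section | Trigger | Consequence |
|---|---|---|
| 5.5.5 | continued missed or incorrect dosing | should leave the trial |
| 7.2 | lack of compliance | IMP stops; child may stay in follow-up |
| 7.3 | consent withdrawal, loss to follow-up, death | leaves the trial; non-compliance not listed |
| 9.4 | none; all randomised children | analysed under treatment policy |

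Section 5.5.5 is the only one of these that removes a child from the trial for non-compliance.

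**2. Reproducing Table 8**

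Inputs from sections 9.4 and 9.9: 30 per arm, two-sided Mann-Whitney test at 0.05, normal scores, 10% missing values replaced from controls.

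Without missing values, power ≈ Φ(Δ/(SD·√(2/n′)) − 1.96). Here n′ = 30 × 0.955 = 28.65, where 0.955 is the efficiency of the Mann-Whitney test relative to the t-test. A simulation (20,000 runs, unstratified test) takes three missing per arm, each replaced by a random control value.

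| Difference / SD | Formula | Simulated, none missing | Table 8 | Simulated, 10% missing | Table 8 |
|---|---|---|---|---|---|
| 15 / 15 | 96.6% | 96.1% | >95% | 91.4% | >90% |
| 15 / 20 | 81.0% | 79.5% | >80% | 70.3% | >70% |
| 15 / 25 | 62.2% | 60.6% | >62% | 51.0% | >50% |
| 11.5 / 15 | 82.7% | 80.8% | >80% | 71.4% | >70% |

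Table 8 reproduces to within about 1.5 points, so the sample-size figures are not at fault.

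**3. Effect of extra withdrawals in the sirolimus arm**

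If a fraction f of the sirolimus arm receives control draws, the expected difference is Δ(1 − f).

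- Planned: 15 × (1 − 3/30) = 13.5, as in Table 8.
- Three more (assumed): 15 × (1 − 6/30) = 12.0.
- Six more (assumed): 15 × (1 − 9/30) = 10.5.

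Each child replaced by a control draw costs 15/30 = 0.5 point.

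**4. The relevant comparison: withdrawn or tested at V12**

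Non-adherence properly dilutes a treatment-policy effect. The cost of the rule is therefore the gap between withdrawing these children and testing them. At difference 15 and SD 15, with control draws for those withdrawn:

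| Benefit kept | Three extra: withdrawn / tested | Loss | Six extra: withdrawn / tested | Loss |
|---|---|---|---|---|
| all | 84.4% / 91.0% | 6.6 | 73.3% / 90.9% | 17.6 |
| half | 84.4% / 87.6% | 3.2 | 73.3% / 83.1% | 9.8 |
| none | 84.4% / 83.0% | none | 73.3% / 71.1% | none |

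In the other Table 8 scenarios, three extra withdrawals with all benefit kept cost:

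- 15 / 20: 69.9 − 59.3 = 10.6 points
- 15 / 25: 50.4 − 42.0 = 8.4 points
- 11.5 / 15: 71.9 − 61.7 = 10.2 points

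With no benefit kept, the loss is again about zero in each.

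**5. If a 1-year score exists**

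The regression rule in 9.4 then uses the child's own 12-month result. Assuming full benefit and a correlation of 0.7 between the 1-year and 2-year scores, power with three extra withdrawals at 15 / 15 is about 90%. That is close to the 91% obtained by testing.

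**The case against.** Chapter 7 governs discontinuation and points the other way; 5.5.5 is a single sentence, says should, and applies only after counselling has failed. A site that follows chapter 7 loses nothing. This stands in part: loss of the V12 score is what 5.5.5 prescribes, not a certain outcome. The contradiction remains, because 5.5.5 is where sites look for the handling of non-compliance.

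Four stronger readings are tempting, and the documents do not support them:

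- **That the 10% allowance left these withdrawals out.** Section 9.9 applies 10% to missing values and counts early termination among them. Nothing places non-compliance outside it, so the three or six extra cases are an assumption.
- **That every withdrawn child is scored as a control.** After titration, visits are quarterly. Non-compliance found at 6 months and repeated at 9 and 12 months reaches the rule at V8, when the 1-year BSID-III is due. For such children the regression rule applies, and 0.5 point per child is an upper figure.
- **That the missingness is tied to tolerability.** Section 5.5.5 defines non-compliance by dosing alone; interruptions for toxicity have their own rules in sections 5.5.3 and 7.1.
- **That the result could be falsely favourable.** Section 9.4 uses control values in order to be conservative, and if sirolimus helps they pull the effect towards zero. No inflation of the type I error is shown.

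**Conclusion.** Section 5.5.5 contradicts 7.2, 7.3 and 9.4 and should be corrected. Followed as written, it produces avoidable missing primary data in the sirolimus arm only and puts control-based values where a treatment-policy estimand calls for observed ones. The harm is an attenuated effect and a departure from the stated estimand.

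Its size is modest and uncertain. With three extra withdrawals at difference 15 and SD 15, the loss against testing at V12 is about 0 to 7 power points. It is near 7 only if the children keep full benefit and have no 1-year score, and near 0 if they keep none or if a 1-year score carries most of the information. The upper end is larger at the higher SDs, at the smaller difference or with six withdrawals. All of this rests on an assumed withdrawal count, an assumed retained benefit and an unstratified test. The contradiction itself rests on none of these assumptions.

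**What to change.** - **Section 5.5.5:** replace withdrawal from the trial with a statement that non-compliance does not by itself end participation, and that the child is followed to the V12 BSID-III unless the guardians withdraw consent to follow-up. Sections 1.3.10 and 6.5 already do this after a negative risk-benefit evaluation.
- **Section 7.2:** state that follow-up to V12 is the default once IMP has been stopped, except after withdrawal of consent, loss to follow-up or death. A blanket change from may remain to remain would not work, because those three events are in the same list.
- **Left unchanged:** whether IMP is stopped, and the visits and safety monitoring while a child is on IMP, stay with the existing clinical sections. Section 7.2 gives the control-group visits only to children whose IMP has been discontinued, and the new wording should not extend them to children still on drug.

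The cost is a few sentences in the next amendment and a notice to sites. A missed 24-month test cannot be recovered later, so the change is worth making while children are still in follow-up.

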### 5.6 Concomitant Medication and Therapy

A concomitant medication is any treatment received by the subject concomitantly to the IMP. Therapy of TSC manifestations according to SOC will not be affected by the trial, except for manifestations requiring mTOR inhibitor treatment (e.g. SEGA). Treatments in addition to the study medication should be kept to a minimum during the trial. However, if these are considered necessary for the subject's health and are unlikely to interfere with the IMP, they may be given at the discretion of the investigator, with a stable dose (if possible). Any treatments, which are initiated, continued and/or changed during the trial, must be recorded in the source data and in the eCRF. Medication taken after informed consent is obtained but before the first dose of the study medication will be documented as prior medication. Medication taken after the first dose of the study medication has been administered will be documented as concomitant medication.

|                                                                    |                                              |                                |
|--------------------------------------------------------------------|----------------------------------------------|--------------------------------|
| Clinical Trial Code: PROTECT
EU trial number: 2022-502332-39-00 | Trial Protocol
(Version 06; (01.10.2024)) | Page 64 of 110
CONFIDENTIAL |
|--------------------------------------------------------------------|----------------------------------------------|--------------------------------|

Caregivers will be instructed not to administer any medications (over-the-counter or other products) during the treatment period without prior consultation with the investigator. The investigator should instruct caregivers to inform the study site of any new medications taken by the study participant after initiation of treatment with the study medication.

If concomitant drugs (other than study drug) are administered, these must be recorded in the subject file and in the eCRF, stating:

- The type (preferably the generic name / International Nonproprietary Name (INN), or trade name)
- The route of administration
- The regimen, including dosage schedule, daily dose (if not indicated by the type), and form of application
- The indication (heart, infection, neuro, other)
- The duration

Additional treatments, including rescue medication for e.g. prolonged seizures, will be administered according to SOC.

**Additional pre-dose blood samples for determination of sirolimus concentrations should be collected one weeks after starting or changing the dose of a CYP3A4 inducer/inhibitor.**

#### 5.6.1 Interaction with other medicinal products

The following paragraph is extracted and adopted from the "Rapamune - EPAR - Product Information, ANNEX I, SUMMARY OF PRODUCT CHARACTERISTICS, section 4.5" of the "European Medicines Agency" as of 25.07.2022 [93]:

"Sirolimus is extensively metabolized by the CYP3A4 isozyme in the intestinal wall and liver. Sirolimus is also a substrate for the multidrug efflux pump, P-glycoprotein (P-gp) located in the small intestine. Therefore, absorption and the subsequent elimination of sirolimus may be influenced by substances that affect these proteins. Inhibitors of CYP3A4 (such as ketoconazole, voriconazole, itraconazole, telithromycin, or clarithromycin) decrease the metabolism of sirolimus and increase sirolimus levels. Inducers of CYP3A4 (such as rifampin or rifabutin) increase the metabolism of sirolimus and decrease sirolimus levels. Co-administration of sirolimus with strong inhibitors of CYP3A4 or inducers of CYP3A4 is not recommended."

